## **12.7. ADVERSE EVENT ANALYSIS**

Adverse event analysis will be performed on the safety population. Adverse Events (AEs) will be mapped to preferred term and body system using the Medical Dictionary for Regulatory Activities (MedDRA). Adverse Event listings will be provided for all AEs, SAEs, and all UADEs leading to study discontinuation.

The number and percentage of patients experiencing AEs will be summarized by treatment group overall and for each System Organ Class and Preferred term. This analysis will be repeated for Serious AEs and for any AEs leading to treatment/study discontinuation. AEs will also be tabulated by maximum severity experienced. Treatments will be compared on incidence of AEs using Fisher's Exact Test.

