## **9.2. SERIOUS ADVERSE EVENTS**

Any Adverse Event, whether considered study-treatment related or not, which fits any of the criteria below, is considered a serious adverse event (SAE):

- Results in death
- Is life-threatening (meaning that the patient was at risk of death at the time of the event; this does not refer to an event which might have caused death if it had occurred in a more severe form)
- Requires in-patient hospitalization or prolongs the existing hospitalization
- Is a persistent disability/incapacity
- Is a congenital anomaly or birth defect
- Is considered an important medical event by the Principal Investigator (e.g., surgery, return to ICU, emergency procedures)

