**9.7.2. RANDOMIZATION THROUGH END OF STUDY**

All adverse events that occur from the time of randomization/enrollment will be recorded as follows:

- Serious Adverse Events (identified in 9.2) will be recorded until Day 60 after randomization, death, or patient withdrawal of study consent, whichever occurs first.
- Non-serious adverse events will be recorded until Day 60 after randomization, death, patient withdrawal of study consent or until hospital discharge, whichever occurs first.

Any serious adverse event (regardless of relationship to the treatment) occurring from the time of enrollment/randomization through end of study must be reported to CytoPherx Inc, or designee, within 24 hours of knowledge of the event. This includes patients in the control arm.

Each clinical trial site will be supplied with written SAE reporting instructions, SAE reporting forms and contact information for reporting of serious adverse events.

For any AE that is ongoing at the time of the initial report, periodic follow-up information will be required until the adverse event is resolved or the patient is no longer in the study, whichever occurs first.

The Investigator is responsible for all adverse events reporting to the Institutional Review Board (IRB) according to the requirements of the IRB and for providing clinical trial monitors with all medical records needed to source-verify the adverse events.

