## 12.2. DETERMINATION OF SAMPLE SIZE

The efficacy null and alternative hypotheses to be assessed are as follows:

$$H_0: \lambda_{C+S} = \lambda_C$$

vs.

$$H_1: \lambda_{C+S} \neq \lambda_C$$

where  $\lambda_{C+S}$  and  $\lambda_C$  are the true 60 day mortality hazard rates for the CRRT+SCD and CRRT alone groups, respectively. The null hypothesis will be tested at the overall two-sided 0.05 level of significance at 80% power. Under the assumptions:

1.  $\lambda_C = 0.01155$  when time to mortality is measured in days (leading to a 50.0% mortality rate at 60 days for CRRT alone);  $\lambda_{C+S} = 0.00718$  when time to mortality is measured in days (leading to a 35.0% mortality rate at 60 days for CRRT + SCD);
2. As described in the SCD-003 Protocol, CytoPherx has assumed a mortality rate of 50% for control and 35% for SCD.

For the control mortality estimate, a 2004 publication [20] was used which summarized mortality data for subjects with acute renal failure (ARF) requiring renal replacement therapy (RRT) in the intensive care unit. A table from this publication is reproduced below (Table 9). In this table, the mortality of subjects who received CRRT (“Dialysis”) is compared to those who did not (“% Mortality No Dialysis”). A weighted average was calculated by weighting the observed value for “% Mortality Dialysis” by the number of subjects enrolled. We found that the weighted mortality of subjects who received CRRT was 58.3%, based on this literature analysis of 5,810 subjects.

| Variable          | Ref. | Year | N    | Location                    | % Mortality No Dialysis | % Mortality Dialysis |
|-------------------|------|------|------|-----------------------------|-------------------------|----------------------|
| Brivet et al      | [26] | 1996 | 360  | Multicenter, France         | 43%                     | 64%                  |
| Liano et al       | [5]  | 1998 | 748  | Multicenter, Spain          | 53%                     | 79%                  |
| De Mendonca et al | [27] | 2000 | 1411 | 16 countries, Europe        | NA                      | 44%                  |
| Silvester et al   | [28] | 2001 | 299  | Multicenter, Australia      | NA                      | 47%                  |
| Metniz et al      | [7]  | 2002 | 839  | Multicenter, Austria        | 39%                     | 63%                  |
| Clermont et al    | [29] | 2002 | 254  | Pittsburgh, USA             | 23%                     | 57%                  |

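### The overall SAE comparison in Section 12.7 counts deaths as SAEs, so a survival benefit can conceal a real excess of non-fatal SAEs with the SCD

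*Protocol*

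**What the plan says.** Section 12.7 (safety analysis set) fixes the summary measure: "The number and percentage of patients experiencing AEs will be summarized by treatment group overall", and by System Organ Class and preferred term. It continues "This analysis will be repeated for Serious AEs" and for AEs leading to discontinuation, and ends with "Treatments will be compared on incidence of AEs" by Fisher's exact test. It does not separate fatal from non-fatal SAEs and names no comparison tied to time at risk or to the treatment period.

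Three other places bear on this:

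- Section 9.2: the first criterion for an SAE is "Results in death".
- Section 9.7.2: "Serious Adverse Events (identified in 9.2) will be recorded until Day 60 after randomization, death, or patient withdrawal of study consent, whichever occurs first". For non-serious events, recording ends at day 60 or at "death, patient withdrawal of study consent or until hospital discharge, whichever occurs first".
- Section 12.2: the control hazard of 0.01155 per day is described as "leading to a 50.0% mortality rate at 60 days for CRRT alone". The SCD hazard is 0.00718 per day, giving 35.0%.

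Section 6.4 limits study therapy to 168 hours.

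**The concern.** A safety comparison should show whether the device adds harm. In the line for patients with any SAE, each death counts as an event, so the arm with fewer deaths starts with a lower percentage whatever the device does otherwise. The trial is designed on the expectation that this arm is the SCD arm, by 15 percentage points. A genuine device-related excess of non-fatal SAEs must overcome that head start before it shows at all.

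An opposite and weaker effect acts on the non-fatal terms. SCD patients who live longer have longer in which to have an event, so at equal daily risk a somewhat higher share of them will have one.

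Patient safety is part of the secondary objective (Section 3.2), and Section 11 asks the DSMB to assess AE incidence. A reader of the overall SAE line could be falsely reassured about the device.

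**Working it through.** **Inputs.** Death hazards 0.01155 and 0.00718 per day and 172 patients per arm (Section 12.2); treatment up to 168 hours (Section 6.4); pilot counts of 23/35 subjects with an SAE (Table 7) and 11/35 deaths by day 60 (Table 8). The protocol gives no AE, SAE or discharge hazards for this trial, so those below are assumptions shown as ranges.

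**The plan's own figures.** 1 − exp(−60 × 0.01155) = 0.500 and 1 − exp(−60 × 0.00718) = 0.350, as stated.

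**Masking, simple form.** Let p and x be the shares of control and SCD survivors with a non-fatal SAE. The any-SAE percentages are 0.50 + 0.50p and 0.35 + 0.65x. They are equal when x = (0.15 + 0.50p)/0.65.

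| Control p | Any SAE, both arms | SCD x | Hidden excess x/p |
|---|---|---|---|
| 20% | 60% | 38.5% | 1.9 |
| 30% | 65% | 46.2% | 1.5 |
| 50% | 75% | 61.5% | 1.2 |

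**Anchor in the pilot.** If all 11 deaths were SAEs, (23 − 11)/(35 − 11) = 12/24 = 50% of survivors had a non-fatal SAE. Taken as the control figure, this is the last row, 1.2-fold. The pilot patients were SCD-treated, so 50% can also be taken as x. Any SAE is then 0.35 + 0.65 × 0.50 = 67.5%, control p = (0.675 − 0.50)/0.50 = 35%, and the hidden ratio is 0.50/0.35 = 1.43.

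**Masking, hazard form.** With a constant non-fatal SAE hazard h in control and kh with the SCD, any SAE = 1 − exp(−60(h + λ)) and non-fatal = h/(h + λ) × (1 − exp(−60(h + λ))), using kh for the SCD arm. The excess is fully hidden at k = 1 + (0.01155 − 0.00718)/h: 1.87 for h = 0.005 and 1.44 for h = 0.01. At 172 per arm, two-sided 0.05, the chance that Fisher's test flags the SCD as worse on non-fatal SAEs is in the last column.

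| h | k | Any SAE, control vs SCD | Non-fatal, control vs SCD | Fisher on non-fatal |
|---|---|---|---|---|
| 0.005 | 1.0 | 63.0% vs 51.8% | 19.0% vs 21.3% | 5.8% |
| 0.005 | 1.5 | 63.0% vs 58.6% | 19.0% vs 29.9% | 61% |
| 0.005 | 1.87 | 63.0% vs 62.9% | 19.0% vs 35.6% | 92% |
| 0.01 | 1.44 | 72.6% vs 72.6% | 33.7% vs 48.4% | 77% |

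In the first row, with no true difference in the non-fatal hazard, the any-SAE comparison is significant in favour of the SCD 51% of the time. In the second, a true 1.5-fold excess still looks favourable.

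**Longer survival.** Mean days alive to time T = (1 − exp(−λT))/λ.

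| T | Control | SCD | Ratio |
|---|---|---|---|
| 60 days | 43.3 | 48.7 | 1.126 |
| 28 days | 23.9 | 25.4 | 1.060 |
| 7 days | 6.72 | 6.83 | 1.015 |

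At equal hazards, a control non-fatal SAE percentage of 5%, 10% or 20% by day 60 becomes 5.6%, 11.2% or 22.4% with the SCD. If deaths fall earlier, as in the pilot (9 of 11 by day 28, assumed uniform within each period), the mean death day is 9/11 × 14 + 2/11 × 44 = 19.5. Days alive to day 60 are then 39.7 and 45.8, a ratio of 1.15.

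**Non-serious events.** Discharge also ends recording. Adding assumed discharge hazards to λ, the SCD-to-control ratio of percentages at equal AE hazards is 1.05 to 1.09 with 0.02 per day in both arms, 0.99 with 0.02 vs 0.025, and 0.90 to 0.94 with 0.02 vs 0.03.

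**The case against.** **The percentage is a legitimate measure.** A patient who has died cannot have a further event, so nothing goes unrecorded after death. With few withdrawals expected (Section 12.5), the share with a non-fatal SAE by day 60 estimates cumulative incidence with death competing. This stands. A reader might infer that the percentages are invalid and should give way to rates per patient-day, but the documents do not support that. Such rates have a weakness of their own: for events confined to the first 7 days, a true 1.10-fold excess divided by days alive to day 60 becomes 1.10 × 1.015/1.126 = 0.99.

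**Inflation of non-serious AEs.** A reader might also infer that a mortality benefit raises the SCD arm's non-serious AE rates. Section 9.7.2 stops that recording at discharge, and quicker discharge with the SCD would cancel or reverse the effect. The direction cannot be stated.

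**Other displays reveal part of the excess.** Preferred-term tables, severity, listings, causality assessment and the separate mortality analysis all help, and the DSMB need not rely on significance (Section 12.8). This limits the masking mainly to the overall SAE line and to terms that mix fatal and non-fatal events. It does not repair that line. That Fisher's test covers SAEs is read from the order of sentences in Section 12.7.

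**The statistical analysis plan may add tables.** It may, and it is not available here. But the point is not an omission: the protocol itself names the measure and the test.

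**Conclusion.** The point holds for the overall SAE comparison. Under the protocol's own 50% vs 35% mortality, it can show equality while non-fatal SAEs among survivors are about 1.2- to 1.9-fold more frequent with the SCD, for assumed control-survivor rates of 50% down to 20%. The pilot figures point to about 1.2- to 1.4-fold, if every pilot death was an SAE. If the mortality benefit is smaller than designed, the masking shrinks with it.

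The effect of longer survival on non-fatal SAE percentages is secondary: up to about 13% relative over 60 days under constant hazards and about 1.5% within the treatment period. No direction is claimed for non-serious events. The primary efficacy analysis is untouched. Section 12.7 should be corrected because the device's safety reading depends on it.

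**What to change.** In Section 12.7:

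1. Tabulate fatal and non-fatal SAEs separately. Make the between-arm SAE comparison on patients with a non-fatal SAE, and report deaths on their own.
2. Add a comparison of AEs and SAEs over a fixed window, the same in both arms, that covers the 168-hour treatment period. Define it by elapsed time and not by time actually on therapy, since Section 7.2 allows therapy to end early for improvement as well as for harm.
3. Present the day-60 non-fatal SAE percentages as cumulative incidence with death as a competing event. Rates per patient-day may be added as supportive, but should not replace the percentages.

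The cost is a few extra tables and a short change of wording. Deaths, hospital discharge and adverse events with their timing are already collected, so no visits, patients or procedures are added.

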## **12.8. INTERIM ANALYSIS/ADAPTIVE DESIGN**

There will be one formal interim efficacy analysis on the primary endpoint of time to all-cause mortality by 60 days, to be inspected by the DSMB. This analysis will be performed on the ITT analysis set after 50% of the planned number of patients achieved 60 day follow-up (or would have achieved 60 day follow-up at the time if the patient did not die or prematurely withdraw). Using the Lan-DeMets function with the O'Brien-Fleming philosophy, the two-sided treatment comparison significance levels to be used at the interim and final analysis are 0.00305 and 0.049, respectively. If the DSMB recommends stopping the study at the interim analysis (i.e., if the two-sided p-value for the primary endpoint is below 0.00305 at the interim analysis), a decision to stop the study will only be made after consultation with the FDA.

If the DSMB does not recommend stopping the study at the interim analysis for overwhelming efficacy, the DSMB may recommend stopping the study for futility if the interim estimate of survival for the CRRT alone group is larger than that for the CRRT + SCD group (in which case, no further enrollment of patients will be carried out, but patients already enrolled at the time of the decision to stop for futility will continue to be followed for 60 days. Otherwise, the DSMB will be presented with a proposed increase in sample size for achieving a statistically significant treatment difference on the primary endpoint by the time of the final analysis. The sample size re-estimation will be performed based on the approach suggested by Cui, Hung and Wang (1999) using the ratio of the initial estimate of effect size,  $E_0$ , which is the difference between Kaplan-Meier estimates of 60 day mortality rate (CRRT + SCD minus CRRT alone) for the initial sample size determination used for study design, and the observed effect size,  $E$ , which is the treatment difference in estimated Kaplan-Meier estimate of the 60 day mortality rate at the time of the interim analysis.

The number of patients initially estimated,  $N_o$  (=172), is readjusted to determine the new total number of required patients,  $N$ , using the following formula:

$$N = \left\lceil \frac{E_o}{E} \right\rceil^2 N_o$$

This method will provide the required number of patients for the second stage of the study. In case the sample size re-assessment results in an increase of the number of subjects, the DSMB may recommend changing the study accordingly (if however the increase in sample size is more than twice the number of originally planned subjects, the DSMB may recommend continuing the study until twice the number of originally planned patients are randomized). In case the sample size re-assessment results in an adaption to less than the original planned sample size, the study will be continued as originally planned (until 172 subjects are randomized).

The statistical methodology used to compare treatments at the interim and final analysis is discussed above. The overall type I error of 5% is controlled as has been confirmed by simulations.

The DSMB will periodically review safety data. A DSMB charter will be written outlining the safety data to be inspected periodically by the DSMB. The DSMB may recommend stopping the study for safety issues, and this recommendation does not need to necessarily be based on statistical significance.

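### Section 12.8 caps the interim sample-size increase inconsistently: the trigger is at three times the planned size but the cap is at twice, so read literally a weaker interim result can give a smaller trial

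*Protocol*

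**What the plan says.** Protocol section 12.8 scales the planned size by the squared ratio of the design difference to the observed interim difference in Kaplan-Meier 60-day mortality. The planned size "is readjusted to determine the new total number of required patients", so N in the formula is a total.

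The next paragraph limits the result in brackets. The condition is that "the increase in sample size is more than twice the number of originally planned subjects". The consequence is that "the DSMB may recommend continuing the study until twice the number of originally planned patients are randomized". If N comes out below the plan, the trial runs to its planned size. If N is larger and the bracket does not apply, the DSMB may recommend changing the study to match N.

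The same paragraph opens by saying "This method will provide the required number of patients for the second stage of the study", which sits loosely beside the definition of N as a total.

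Section 12.2 gives 172 randomized per group. The synopsis and section 5.1 give only the initial figure of up to 344 patients. No other section states a maximum after re-estimation.

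**The concern.** The condition is written on the increase, N minus the planned number N0. The consequence is written on the total. An increase above 2 × N0 means a total above 3 × N0, but the cap then imposed is 2 × N0. Totals between two and three times the plan are neither capped nor excluded.

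The proposed size therefore rises as the interim effect weakens, passes the level of the cap, and then drops back to it. A re-estimation rule should be settled before the interim data are seen. Here a DSMB statistician holding, say, a 9-point difference would have to choose between the literal text and the probable intent after seeing the result. The two answers differ by hundreds of critically ill patients.

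**Working it through.** **Inputs.**
- Design mortality, section 12.2: control, "leading to a 50.0% mortality rate at 60 days for CRRT alone"; SCD, "leading to a 35.0% mortality rate at 60 days for CRRT + SCD". Hence E0 = 15 points.
- Design test: "overall two-sided 0.05 level of significance at 80% power".
- N0 = 172 randomized per group (166 evaluable), section 12.2.
- Interim after half the patients: 172 / 2 = 86 per group.

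**The plan's own figure.** The hazard ratio is 0.00718 / 0.01155 = 0.6216, with ln HR = −0.4754. At the final two-sided level of 0.049 and 80% power, the Schoenfeld formula gives 4 × (1.969 + 0.842)² / 0.4754² ≈ 140 events. Dividing by the summed event proportions, 0.50 + 0.35, gives 164.7, so 165 per group. The stated 166 is reproduced closely, and the base of the rule is sound.

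**Where trigger and cap fall.** N / N0 = (15 / E)².
- Trigger as written: N − N0 > 2 × N0, so N > 3 × N0, so E < 15 / √3 = 8.66 points.
- Level of the cap: N = 2 × N0, reached at E = 15 / √2 = 10.61 points.

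The uncapped window is therefore 8.66 to 10.61 points.

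**Size by interim difference (N0 = 172 per group).**

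| E (points) | Formula N per group | Increase | Literal rule, per group (both groups) | Total capped at 2 × N0, per group (both groups) |
|---|---|---|---|---|
| 12 | 269 | 97 | 269 (538) | 269 (538) |
| 10 | 387 | 215 | 387 (774) | 344 (688) |
| 9 | 478 | 306 | 478 (956) | 344 (688) |
| 8.67 | 515 | 343 | 515 (1,030) | 344 (688) |
| 8.65 | 517 | 345 | 344 (688) | 344 (688) |
| 8 | 605 | 433 | 344 (688) | 344 (688) |

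The literal maximum is 3 × 172 = 516 per group, or 1,032 patients. The drop at 8.66 points is 516 − 344 = 172 per group, or 344 patients. At 9 points the two readings differ by 956 − 688 = 268 patients.

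**Chance of landing in the window.** Normal approximation, 86 per group, SE = √[(p1(1 − p1) + p2(1 − p2)) / 86].
- 50% v 35%: SE = 7.45 points. P = Φ((10.61 − 15) / 7.45) − Φ((8.66 − 15) / 7.45) = 0.080.
- 50% v 38%: 0.098.
- 50% v 40%: SE = 7.55 points, P = 0.102.
- 50% v 50%: SE = 7.62 points, P = 0.046 (SCD-favouring side).

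Early stopping does not empty the window. The top of it is about 10.61 / 7.45 = 1.4 standard errors, well short of the roughly 2.96 that corresponds to 0.00305. The difference also favours SCD, so the futility rule does not apply.

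**Total or second stage.** If N were the second-stage number, the interim 86 per group would be added. At 9 points that means 564 rather than 478 per group. The gap is not constant. At 8 points both readings trigger the cap and give 344. At 18 points the formula gives 119, so the total reading is floored at 172 while the other gives 119 + 86 = 205, a difference of 33.

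**The case against.** The strongest reply is that this is a drafting slip: the writer meant that the increased sample size should not exceed twice the plan. Under that reading the rule is monotone, the maximum is 688, and the awkward window disappears. That is probably the intent, but nothing in the protocol says so. Reading both parts as an increase of 2 × N0 would be equally coherent and would give a maximum of 1,032.

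Other points deserve weight:
- **Error control.** A reader might infer that the ambiguity undermines the statement that simulations confirmed the 5% level. The documents do not support this. Section 12.5 combines the two stages with pre-specified equal weights, and with fixed weights type I error does not depend on which second-stage size is chosen.
- **1,032 patients.** A reader might infer that the plan commits to this number. It does not. It is the most the literal rule can propose, at almost exactly 8.66 points, and both steps are recommendations by an advisory board.
- **Total or second stage.** A reader might infer a fixed 172-patient discrepancy. The floor and cap can shrink or remove it, and the definition of N together with the floor at the planned size points to a total. The sentence is loose rather than a second contradiction of equal weight.
- **Base of 172.** Section 12.8 omits 'per group'. Taken as a total, the literal maximum would be 516 patients, with the same non-monotone shape. Section 12.2 supports per group.
- **Brackets in the formula.** If they meant rounding the ratio up to a whole number, every increase would be at least fourfold and capped, leaving the window empty. But N could then never fall below the plan, which section 12.8 expressly provides for. This reading is not credible.
- **Reach.** Outside the window both cap readings agree, so roughly 90% or more of interim results are unaffected.

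**Conclusion.** The point holds as an internal inconsistency in a stated decision rule. Trigger and cap refer to different quantities, and followed as written an interim difference of 8.66 to 10.61 points gives 344 to 516 per group, while a weaker result gives 344. The chance of meeting this is about 5% to 10% across the scenarios examined. The consequence is up to 344 patients beyond a 688 cap.

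This rests on 172 being per group, an interim at 86 per group, control mortality of 50%, and a normal approximation to the interim difference. The non-monotone shape depends on none of these. What is affected is the size of the trial and the coherence of the rule, not the validity of the final test. Any power, expected-size or maximum-size figure does depend on which version of the rule was used. The text should be corrected before the interim analysis.

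**What to change.** Replace the bracket in section 12.8 with: *N is the new total per group; if N exceeds twice the originally planned number per group, N is set to twice that number (344 per group, 688 in all), which is the maximum.* Reword the second-stage sentence as: *second-stage patients = N minus the interim cohort.* If the sponsor in fact intended a larger maximum, it should be stated on the same quantity as its trigger.

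Carry the same wording into the DSMB charter, and check that any quoted power, expected size or maximum size was computed under this rule.

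The cost is two sentences and a check of existing calculations. It adds no patients or procedures.

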| Approximate Number of Subjects    | Up to 344 patients will be enrolled in this study.                                                                                                                                                                                                                                                                         |
| Approximate Number of Centers     | Up to 30 Clinical Centers in the United States will participate in this study.                                                                                                                                                                                                                                             |
| Duration of Subject Participation | Each patient will be followed for 60 days following randomization.                                                                                                                                                                                                                                                         |
| Inclusion Criteria                | 
 
1. A patient, or legal representative, has signed a written informed consent form.
 
2. Must be receiving medical care in an intensive care unit (e.g., ICU, MICU, SICU, CTICU, Trauma).
 
3. Age 18 to 80 years.
 
                                          |

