## **5. SELECTION OF PATIENT POPULATION**

### **5.1. PATIENT RECRUITMENT**

Up to 30 Clinical Centers in the United States will enroll up to 344 patients to participate in this clinical trial. Patients receiving care in the Intensive Care Units of each participating hospital will be screened daily and identified for participation in the trial.

All patients that are screened for the study will be entered by the Study Staff on a screening log. If the patient is not enrolled, the screening log will include information explaining why enrollment did not take place (exclusion criteria, attending physician refusal, patient refusal, etc).

All enrolled patients will receive standard intensive care treatment for patients undergoing CRRT or CRRT + SCD. Any mode of CRRT will be allowed (CVVH, CVVHD, and CVVHDF) following each participating clinical site's protocol. The modality of CRRT is not expected to affect performance of the SCD.

The Sponsor will provide each site with a CRRT device (B.Braun Diapact® CRRT System) to be used with each patient randomized either to the Control or Study Arms. The B.Braun® CRRT System is a compact, self-containing system for high-flow continuous or intermittent renal therapies. Some of the technical features of the Diapact include an integrated plate warmer for the heating of infusion and dialysate fluids and a single load cell weighing system which reduces the possibility of error and increases accuracy. The Sponsor will also provide all the tubing, SCD-ARF and hemofilters to be used during the observation period of this trial.

Each participating clinical site is to use their regional citrate anticoagulation protocol for the CRRT and SCD-ARF circuits (Study Arm) and for the CRRT only (Control Arm). The recommended ionized calcium level (measured post

SCD-ARF) in the CRRT and SCD-ARF blood circuit should be between 0.25 and 0.4 mmol/L.

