Then the required evaluable sample size is 166 subjects per group. To account for attrition, which is expected to be minimal, 172 subjects per group will be randomized. The sample size was calculated using the PASS 2008 software, taking into account the fact the study may be stopped for overwhelming efficacy at the interim analysis using the log-rank test at the O'Brien-Fleming significance level of 0.00305.

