#### 12.5. PRIMARY ENDPOINT

The primary endpoint in this trial is time to mortality through 60 days post-randomization. The Kaplan-Meier curve of time (days) to mortality through 60 days post-randomization will be presented, as will the Kaplan-Meier estimate of the 60 day mortality rate. In addition, the raw number and percentage of subjects who died by 60 days will be presented by treatment group. Treatment groups will be compared on time to mortality through 60 days using the log-rank test. The analysis will be carried out for the ITT (primary) and Per-Protocol (secondary) analysis set. It is anticipated there will be few randomized subjects who prematurely withdraw from the trial. Subjects who do not die will be censored at 60 days or at the last known time alive, whichever is earlier.

Due to one formal interim efficacy analysis following which the DSMB may recommend an increase in sample size (based on the observed treatment difference seen at the interim analysis) beyond the initially planned 172 randomized patients (see Section 12.8 for details), the final analysis comparing treatments on the primary endpoint does not use the conventional log-rank test p-value to determine if a statistically significant treatment difference exists. Instead it uses a weighted test statistic,  $T^*$ , proposed by Cui, Hung and Wang [33] in which the independent test statistics of the two stages (interim and final) are combined by pre-specified weights,  $w_1$  and  $w_2 = 1 - w_1$ , where  $w_1$  is the proportion of the total *initially* planned number of patients at which the interim analysis is performed. In the present case the trial is designed for 172 randomized subjects per group with an interim analysis after 50% of the patients achieve 60 day follow-up (or would have achieved 60 day follow-up had they not died or prematurely withdrawn). Thus, the planned information time proportions are  $w_1 = 50\%$  for first stage and  $w_2 = 1 - w_1 = 50\%$  for the second stage.

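### Sections 12.5 and 12.8 use 172, the per-group size, as if it were the trial total, and the enrolment limit of 344 leaves no room for the adaptive increase

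*Protocol*

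**What the plan says.** **The plan.** Section 12.2 derives 166 evaluable subjects per group and, allowing for attrition, states that "172 subjects per group will be randomized". With 1:1 allocation that is 344. One sentence of Section 12.5 repeats 172 per group.

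**The adaptive rules.** These drop the words per group:

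- Section 12.5 speaks of an increase "beyond the initially planned 172 randomized patients".
- Section 12.5 also defines t1 and t* as ratios to the initially planned total, and gives that total as 172 both times.
- Section 12.8 sets N0 = 172, which "is readjusted to determine the new total number of required patients".
- If re-estimation gives a smaller number than planned, Section 12.8 says that "the study will be continued as originally planned (until 172 subjects are randomized".
- If the increase is more than twice the planned number, Section 12.8 says that "the DSMB may recommend continuing the study until twice the number of originally planned patients are randomized".

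**The enrolment limit.** The synopsis says "Up to 344 patients will be enrolled in this study", and Section 5.1 says that up to 30 centers "will enroll up to 344 patients to participate in this clinical trial". Neither mentions the adaptive increase, and no other section says that the limit excludes it.

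**The concern.** The floor, the re-estimated size and the ceiling are the three numbers that the DSMB needs once it has seen the interim treatment difference. On either reading of 172, one of them conflicts with another part of the protocol. If 172 is the total, the floor and the cap contradict Section 12.2. If 172 is per group, they agree with Section 12.2 but exceed the stated enrolment. A conflict settled only after the interim would be settled by people who know the effect, and the planned weighting and prespecified rules are there to avoid that.

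**Working it through.** **Inputs (Section 12.2 unless noted).** Daily hazards 0.01155 and 0.00718, that is 60-day mortality of 50% and 35%; planned difference E0 = 15 points; log-rank test; "overall two-sided 0.05 level of significance at 80% power"; two-sided levels 0.00305 (interim) and 0.049 (final); interim at 50% of planned patients (Section 12.8).

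**1. Reproduce the plan's own figure.**

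- ln HR = ln(0.00718/0.01155) = −0.4754.
- Deaths = 4(1.969 + 0.842)² / 0.4754² ≈ 140.
- Mean mortality = (0.50 + 0.35)/2 = 0.425.
- 140/0.425 = 329 patients, or 165 per group. The plan has 166.
- The Lan-DeMets O'Brien-Fleming levels at half information also reproduce: 0.00305 and 0.0490.

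So 166 and 172 are per-group numbers.

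**2. Power by total size.** Deaths = 0.425 × total. Power allows for both looks and treats every patient counted as evaluable.

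| Total | Deaths | Power |
|---|---|---|
| 332 (evaluable plan) | 141 | about 80.5% |
| 344 (randomized plan) | 146 | about 82% |
| 172 (literal floor) | 73 | about 53% |

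**3. The re-estimation rule, N = (E0/E)² × N0, on the two bases.**

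| | 172 as total | 172 per group (344 total) |
|---|---|---|
| Floor | 172 | 344 |
| N at E = 12 points | (15/12)² × 172 = 268.75, so 269 | (15/12)² × 344 = 537.5, so 538 |
| Cap at twice the plan | 344 | 688 |

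With 172 as total, an interim effect of 12 points calls for an increase to 269, fewer than the 344 already planned, and the cap equals the original plan. With 172 per group, any observed effect below 15 points gives N above 344, so every increase exceeds the limit in the synopsis and Section 5.1.

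**4. The cap trigger.** Taken literally, an increase of more than twice the planned number means N − N0 > 2N0, or N > 3 × 344 = 1,032, while the cap is 2 × 344 = 688. For E between 15/√3 = 8.7 and 15/√2 = 10.6 points, N lies between 688 and 1,032 and the cap is not triggered on that parse.

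**5. The weighted statistic.** Z(2) depends on t1 and t* only through r = t1/t*. Take a trial that is not enlarged, with information proportional to patients, so that the true r is 0.50.

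- Both counted as totals: (172/172)/(344/172) = 0.50. The 172 cancels.
- Both counted per group: (86/172)/(172/172) = 0.50. The 172 cancels.
- Mixed, t1 per group and t* in total: (86/172)/(344/172) = 0.25.

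In the mixed case, with corr(Z(1), Z*) = √0.5 = 0.707:

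- Var Z(2) = (1 + 0.25 − 2 × 0.5 × 0.707)/0.75 = 0.724.
- Cov(Z(1), Z(2)) = (0.707 − 0.5)/0.866 = 0.239.
- Var T* = 0.5(1 + 0.724) + 0.239 = 1.10, where it should be 1.

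Simulation (2 million trials, both boundaries) gives a two-sided type I error of about 6.1%, against 5.0% with r = 0.50.

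**The case against.** **The intent is plain.** Section 12.2, one sentence of Section 12.5 and the reproduced calculation all say per group, and the floor sentence itself refers back to the original plan. Read per group, the formula, floor and two-fold cap in Section 12.8 agree with one another; only the labels are wrong. This stands. A reader might infer that the trial will be run at half size, but the document does not support that as the likely outcome. The 53% is the design power of a trial of 172, not a forecast for this one.

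**Stopping at the interim.** A reader might also infer that the literal floor ends the trial at the interim, since half of 344 is 172. That takes 344 as the base for the interim and 172 as the base for the floor. If 172 were the total, the interim would fall at 86.

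**The increase is not impossible.** The synopsis row is headed as an approximate number, Section 12.5 calls the size initial, and Section 12.8 lets the DSMB recommend changing the study. An amendment could raise the limit. The supportable statement is narrower: the protocol as written does not permit the increase it provides for, and does not say whether 344 is a starting size or a ceiling.

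**The type I error is not shown to be inflated.** It is inflated only if the two counts are mixed. The definitions invite that by pairing a per-group figure with the word total, but they do not require it.

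**The cap trigger.** It is probably loose wording for an increase to more than twice the plan, and it is a secondary point.

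**Conclusion.** The inconsistency is real and should be corrected before the interim analysis. The figure 172 is mislabelled in one sentence of Section 12.5, in both the t1 and t* definitions, and in the base and floor of Section 12.8. Section 12.2 settles what the floor was meant to be, so that part is a labelling error: taken literally it would mean about 73 deaths instead of 146, and about 53% power instead of 80%.

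The enrolment limit is the part that knowing the intent does not resolve. On the intended reading the cap implies 688, which is 344 more than the synopsis and Section 5.1 allow. No section states 688; it follows from doubling 344.

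The power figures assume the plan's hazards and no attrition. The 6% type I error assumes mixed counting in a trial that is not enlarged.

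**What to change.** - **Section 12.5:** write 172 per group (344 total) wherever 172 appears. Define t1 and t* with numerator and denominator on the same basis, preferably totals over 344.
- **Section 12.8:** set N0 = 344 if N is a total, and the floor at 344 randomized. Apply the cap if N exceeds twice the originally planned number, and state the ceiling as a number. The present text implies 688 in total, which the sponsor should confirm. The DSMB's discretion to recommend can stay as it is.
- **Synopsis and Section 5.1:** describe 344 as the initial planned size and give the adaptive maximum beside it.

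**Cost.** The edits are to wording only and leave the design calculation and boundaries unchanged. They do have one visible consequence: the stated maximum enrolment becomes larger than 344, and doubles if 688 is confirmed. The sponsor has to accept that openly.
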